### Withdrawal and discontinuation

Patient and GP participants can withdraw from the study at any time. Only baseline anonymised information will be retained for analysis once the patient/GP withdraws. If a GP withdraws, his or her patients can still be followed-up individually until the end of the study.

### Intervention arm

The intervention training program will be based on the *Vivre sans tabac* curriculum [6, 7, 20]. The full curriculum has two parts: the first involves a 1.5-h module increasing current knowledge of smoking associated risks and the benefits of pharmacological and non-pharmacological smoking/tobacco cessation aids, modelling the approach to patients at different stages of change (precontemplation, contemplation, and preparation) using video clips. The second part (1-h) involves role-plays practicing the skills learned. In the intervention arm, we will keep the same format (1.5 h interactive module + 1 h of role plays) but will adapt the original content by presenting a quit attempt with a smoking cessation aid as the default to all patients (Table 1) and integrate the use of a decision aid (DA). We will tailor our approach using default choice to various patient scenarios involving current smokers and their reaction to the suggestion of quitting.

**Table 1 Tab1:** Approach to patient smoker profile types in intervention and enhanced usual care groups

**Smoker profile** (stage in Trans-theoretical model [22])	**Current approach **[5] (control group)	**Approach using default choices and a decision aid** (Intervention group)
25-year-old male smoker seen for flu-like symptoms, smokes ≥ 5 cigarettes per day, more evenings and weekends, uninterested in discussing his tobacco use (pre-contemplative)	“What do you know about the risks of smoking?” “What are potential benefits of quitting?”	“Why don’t you return for an appointment next week so we can follow up your flu symptoms and specifically discuss quitting smoking?” “I understand if you’re not sure about quitting, but I can help. You should give treatment, like with varenicline, a try.”
60-year-old female smoker consulting for a urinary tract infection, 20 cigarettes per day, stressful home and work environment, wants to quit but not now (contemplative)	“What is it that you like and don’t like about cigarettes?” “You say that smoking is bad for your health. What barriers do you see to quitting?” “What do you see as the next step?”	“Now is the time to quit smoking. There effective treatments that can help” “I council my patients to try quitting sooner rather than later” “Let’s make an appointment next week to make a detailed plan”
65-year-old male smoker with mild asthma consulting with seasonal allergies, has already tried quitting and is open to trying again (action)	“Congratulations! I propose setting a quit date.” “Have you hear about medications that can help with quitting? I would recommend that you try one.” “If you’d like, we can schedule regular appointments to help you with your symptoms”	“Congratulations! Let’s set a quit date.” “Nearly all of my patients use a medication to help quit. Some use e-cigs. This tool can help us choose the approach that’s right for you.” “My assistant will call you next week to see if you are tolerating the medication and make a follow-up appointment”

The decision aid will be available in both paper and electronic formats based on our previously developed one-page table (Appendix 4) [18]. It is an encounter DA, designed for use during consultations. The paper version uses a large table, with one row for each pharmacologic aid and one column for each characteristic, such as cost, efficacy and adverse effects. The electronic version (www.howtoquit.ch) expands on the paper version to include larger photos, brief videos demonstrating use of the product, and information on prescribing.

### Enhanced usual care arm

The enhanced usual care arm will consist of a 45-min refresher training about smoking cessation that does not aim to change GP behaviour. It will include the same information about pharmacologic quit aids and electronic cigarettes. Most GPs in French-speaking Switzerland have received this level of instruction about smoking cessation previously, making this training course ‘enhanced’ usual care. We say enhanced because the course will augment knowledge of smoking cessation in the short-term, and participation in the study could trigger more discussions about smoking cessation than routine practice. However, given the proven efficacy of the existing *Vivre sans tabac* curriculum that has been widely implemented in Switzerland [6], it is not ethical to perform a sham training program. Further, it will be impossible to have any blinding between groups without at least some training.

Both groups will be given time to complete questionnaires before and after the intervention. They will be trained to identify current smokers eligible for this trial, complete informed consent, and enrol participants for follow-up.

## Outcomes

Patients will be followed-up for six months by the research team. A complete list of all patient-level visits, telephone calls and relevant procedures is summarized in Fig. 3.

**Fig. 3 Fig3:**
[figure not shown]
Diagram of the expected role of participating patients

Follow-up questionnaires at 3 weeks, 3 months and 6 months will primarily be done by telephone, with mailed questionnaires for participants we cannot reach by phone. The content of each questionnaire is detailed in Appendix Table 2.

### Primary outcome measure

The primary outcome measure is smoking cessation. We will measure smoking cessation using the self-reported, 7-day point-prevalence smoking abstinence at six months follow-up after the baseline visit with a GP. Point-prevalence abstinence will be defined as self-reported absence of smoking or use of other tobacco-containing products (smokeless tobacco like iQos, snus, etc.) during the prior 7 days at the time of a follow-up phone call by the research team [21]. The point-prevalence of smoking abstinence at 6 months is a widely used measure in the smoking cessation literature that correlates closely with long-term abstinence. Use of an e-cigarette will not count as tobacco use.

#### Baseline patient and GP factors that may be associated to the primary endpoint

Numerous parameters will be collected from GPs and patients that could influence the difference in smoking cessation between the intervention and control groups. These variables, summarized in Appendix Table 3, will be compared between groups to ensure adequate randomization and allow stratified analyses of the primary result. For patients, we will collect information about socio-demographic characteristics, health literacy, reasons for seeking medical care, smoking behaviours, and baseline motivation to quit smoking. For GPs, we will collect information about socio-demographic characteristics, personal tobacco consumption, practice characteristics, and baseline practices regarding smoking cessation.

### Secondary outcome measures (Appendix Table 4)

Evaluate the effect of the intervention on the proportion of patients who make at least one quit attempts within six months of their baseline visitEvaluate the effect of the intervention on the proportion of patients who use at least one quit aids (pharmacologic, electronic cigarette, or counselling sessions)Evaluate the effect of the intervention on patients’ perceived involvement in discussions about smoking cessationMeasure uptake of key behaviours, notably offering quit aids to all current smokers and use of the electronic decision aid among GPsUnderstand facilitators and barriers to offering patients who smoke smoking cessation aids in primary care, and how default choices and a decision aid influences GP practices

Secondary outcome measures will be reported in relation to our theoretical framework (Fig. 4).

**Fig. 4 Fig4:**
[figure not shown]
Theoretical framework of interventions to use default choices and shared decision making for smoking cessation in primary care, which will change the approach of GPs to current smokers, increase quit attempts, and eventually increase rates of smoking cessation

## Data collection, management and analysis

GPs and patients will complete several questionnaires throughout the study (see Figs. 1 and 3). To address variable levels of literacy and health literacy of trial participants, we will use validated short form questionnaires whenever possible.

### Data management

We will use REDCap to enter all data collected by GPs (paper forms) and data collected by telephone. REDCap software is a secure software hosted on Unisanté servers that allows for collecting and managing data. Source data will be from paper questionnaires, electronic questionnaires, and audio recordings of qualitative interviews, depending on the data collection point (Figs. 1 and 3). Patient paper questionnaires collected by participating GPs will be sent in batches, bimonthly from GPs to the study team at Unisante, where they will be stored in the Investigator Site File (office of the research assistant) in a closed cupboard. Data will be entered into REDCap Case Report Forms. Data collected during telephone interviews will be directly collected on electronic Case Report Forms in REDCap. Audio recordings from qualitative interviews will be transcribed and then deleted. All documents will be stored for 10 years. All study data will be archived for 10 years after study termination or premature termination of the study. Electronic data will be archived on the Unisanté server. No biological material is being collected.

### Statistical methods

Data will be summarized for all patients and by group: intervention vs enhanced usual care. Continuous and count variables will be summarized as mean (95% confidence interval) or median (IQR) and categorical variables as numbers (percent). Binary outcomes at 6 months will be compared between the two arms intervention vs control using a logistic regression model with clustered-robust standard error estimates. To take into account the clustered repeated measurement design in testing the intervention effect and changes over time, repeated measurement outcomes will be analysed using a mixed-effect models. Depending on the distribution of the outcomes, a logistic regression model will be used for binary outcomes while count regression models (Poisson, negative binomial or zero-inflated negative binomial model) will be used for count outcomes. The intervention x time and others potential interactions will be tested in the models. In addition, subgroup analyses (sex, age, …) will be performed to assess in which subgroup the intervention is most effective. Data analysis will be performed using Stata 16 Software (StataCorp. 2019. Stata Statistical Software: Release 16. College Station, Texas: StataCorp LLC) and performed by a senior Biostatistician.

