### Sample size and power calculation

Based on previous research, we expect approximately 4% of current smokers seen with usual care conditions will report having quit smoking at 6 months after a baseline visit (32). This is based on a model whereby 20% of current smokers discuss a quit attempt (higher than usual with Hawthorne effect) (11), 10% get a specific pharmacologic aid or e-cigarette, and 4% successfully quit. We anticipate a 100% increase in the number of quit discussions in the intervention arm, so about 40% of current smokers discuss a quit attempt. Subsequently, 20% will use a pharmacologic aid or e-cigarette, and 10.5% will successfully quit. For the primary outcome will use mixed effect models accounting for clustered, repeated measures; without adjusting for baseline patient characteristics, we will compare two proportions, using a two-sided test for significance, β = 0.80, α = 0.05, and an intraclass correlation coefficient of 0.03. With these parameters, we need 20 clusters (i.e. individual GPs) in each arm, each with 20 current smokers who consent to inclusion. Assuming 15% drop-out or under-recruitment by individual GPs, we will aim to recruit 46 GPs with 23 patients each, so 1,058 patients. Individual GPs will be capped at 25 patients. No specific interim or safety analyses are planned. STATA version 16.0 for Windows (StataCorp LLC, College Station, USA) will be used for all statistical analyses. Stopping rules for the study: Recruitment of GPs will end when 46 have signed a contract to complete the training program and undergone randomization. Patient recruitment will end when all participating GPs have included ≥ 20 patients and 1,060 patients have been recruited overall. GPs will be considered inactive if they have not recruited patients within the last 6 months. The trial will also end if GP recruitment has ceased and all GPs have completed recruitment. If recruitment is too low (< 200 patient participants 12 months after beginning GP training programs), new recruitment strategies will be put in place and the study may be terminated.

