### Randomization

The unit of randomization will be GPs who consent to participate in a smoking cessation training program and subsequently recruit eligible patients. The clinical trial protocol follows the CONSORT diagram in Fig. 1. Randomization, done by the study statistician, will be by blocks of two or four GPs to ensure balance between training dates. GPs from the same practice will be randomized together.

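### The plan names two models for the primary outcome; if the cluster-robust logistic model is the primary test and is left uncorrected, its 5% level is about 6.2% to 6.3%

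*Protocol article*

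**What the plan says.** The primary outcome is binary and measured at one time point: "self-reported, 7-day point-prevalence smoking abstinence at six months follow-up after the baseline visit with a GP".

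Two sections of the protocol article bear on its analysis:

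- **Statistical methods** compares binary 6-month outcomes with "a logistic regression model with clustered-robust standard error estimates". Mixed-effects models are kept there for outcomes measured repeatedly. The section names Stata 16, but no finite-sample correction, no t reference and no clustering unit.
- **Sample size and power calculation** states: "For the primary outcome will use mixed effect models accounting for clustered, repeated measures". This is the only sentence that ties a model to the primary outcome by name.

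The design is set "using a two-sided test for significance, β = 0.80, α = 0.05, and an intraclass correlation coefficient of 0.03" (the 0.80 is evidently power). The result is that "we need 20 clusters (i.e. individual GPs) in each arm, each with 20 current smokers who consent to inclusion", raised to 46 GPs with 23 patients each. The Randomization section adds that "GPs from the same practice will be randomized together".

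**The concern.** A cluster-robust variance is built from the squared residual totals of the clusters. With few clusters those residuals are too small on average, because they are taken around a mean fitted to the same clusters. The estimated variance is also noisy, which a normal reference ignores. Both effects push the test towards rejection and shorten the interval. With 20 to 23 clusters per arm and a quit rate near 4%, the effect is modest but not negligible.

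At stake is whether the two-sided 0.05 in the sample size section is delivered for the headline result. A result just under p = 0.05 could owe its significance to the variance formula and reference distribution. The effect depends on which of the two named models is the primary test, and on how many units were in fact randomised independently.

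**Working it through.** **1. Reproduce the planned size.** Inputs from the sample size section: 4% versus 10.5%, two-sided α 0.05, power 0.80, ICC 0.03, 20 patients per GP.

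- Pooled rate: (0.04 + 0.105)/2 = 0.0725.
- n per arm without clustering: [1.96·√(2·0.0725·0.9275) + 0.8416·√(0.04·0.96 + 0.105·0.895)]² / 0.065² ≈ 249.
- Design effect: 1 + 19·0.03 = 1.57.
- 249·1.57 ≈ 391 per arm, and 391/20 ≈ 19.5, so 20 clusters per arm.

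The stated size reproduces, with power of about 81% at 20 × 20. It is not affected by this point.

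**2. Type I error of the robust logistic test.** Both arms share one quit rate p. Cluster rates are drawn from Beta(p(1−ρ)/ρ, (1−p)(1−ρ)/ρ) and counts are binomial. With p = 0.04 and ρ = 0.03 this is Beta(1.29, 31.04). With arm as the only covariate, the robust variance of the log odds ratio is

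G/(G−1) · Σ over arms of Σⱼ(yⱼ − mp̂)² / [Mp̂(1−p̂)]²,

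where G is the total number of clusters, m the cluster size and M the patients per arm. The uncorrected test compares the Wald ratio with 1.96. The corrected test uses G/(G−2) and t on G−2 degrees of freedom. Independent simulations with 40,000 or 60,000 trials per setting agree. At p = 4% and ICC 0.03:

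| Setting | Uncorrected, z | G/(G−2), t(G−2) |
|---|---|---|
| 40 clusters of 20 | 6.2% to 6.3% | 5.1% to 5.4% |
| 46 clusters of 23 | 6.2% to 6.3% | 5.1% to 5.4% |

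The last column is the range over both designs. At null rates of 7.25% and 10.5% the uncorrected test gives 5.9% to 6.4%. Over an assumed ICC range of 0.01 to 0.05, with 40 to 46 clusters, it gives 5.7% to 6.7%.

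**3. Standard error.** At 4% and ICC 0.03 the mean robust standard error is about 0.94 (40 clusters) to 0.95 (46 clusters) of the true one. As a rough check, P(|Z| > 1.96·0.94) ≈ 6.5% and P(|Z| > 1.96·0.95) ≈ 6.3%, close to the simulated levels.

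**4. Departures from equal GP clusters (assumed inputs, ICC 0.03 unless stated).**

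- Sizes between 5 and 25, within the cap of 25: 6.3% to 6.7% uncorrected.
- Coefficient of variation of cluster size 0.4 to 0.7, cap ignored: 6.2% to 7.5% uncorrected. The simple correction brings this to 5.2% to 5.6% at 0.4 and 5.8% to 6.3% at 0.7. At a mean of 20, a cap of 25 limits the coefficient to √(20·5)/20 = 0.5, so the upper end is not attainable at that mean.
- 30 independent units of equal size, for shared practices: 6.8% to 6.9% at ICC 0.03, and 6.0% to 7.2% over the ICC range 0.01 to 0.05.

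**5. The other named model.** A random-intercept logistic model with a Wald z test (4% rate, ICC 0.03, 4,000 trials per setting) gives 5.6% with 40 clusters of 20 and 5.0% with 46 of 23. The Monte Carlo standard error is about 0.35 points.

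**6. Power.** At 20 × 20, the uncorrected robust test has 81% to 82% and the corrected one 79%.

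**The case against.** Four objections carry weight.

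- **The plan may not use an uncorrected estimator.** The article is silent on the correction and the reference distribution, and such detail may sit in an analysis plan or full protocol that is not shown. A reader might infer from the software named that a default z test will be used; the document does not say so. This stands, and makes the finding conditional. It does not remove it, because the article itself fixes a type of estimator that, as ordinarily applied at 40 to 46 clusters, misses the stated alpha.
- **The robust model may not be the primary test.** A reader might take the Statistical methods sentence as settling the matter, since the primary outcome is binary at 6 months. But the sample size section names mixed models for that outcome, and under them the excess is small or absent. This stands too. The disagreement between the two sections is the firmer part of the finding.
- **The larger figures rest on assumptions.** No section says how many GPs share a practice, and the sample size section defines clusters as individual GPs. A level near 7% shows what could happen and is not a property of the plan.
- **The effect is small.** An excess of about 1 percentage point matters only for results close to the threshold. A reader might conclude that the primary test is unreliable or the trial mis-sized; the calculations support neither. The excess does run in one direction, towards a positive result.

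**Conclusion.** The concern holds in conditional form. The plan gives two models for the primary outcome. If the robust logistic model is the primary test, and is applied without correction and with a normal reference, the nominal 5% level is about 6.2% to 6.3% with 40 to 46 equal GP clusters, and standard errors are about 5% to 6% too small. This rests on the plan's own 4% rate and ICC of 0.03 and on beta-binomial clustering. Unequal recruitment raises the level somewhat. Only 30 independent units, an assumed number, would raise it to about 7%. It cannot be said from the document that the primary test will be uncorrected. The point deserves correction because the remedy is cheap and bears on the headline result.

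**What to change.** 1. Reconcile the Sample size and power calculation section with the Statistical methods section, so that one model is named for the primary outcome.
2. If robust logistic regression is kept, state a small-sample-corrected variance with a t reference on clusters minus 2 degrees of freedom, for both the test and the interval. A G/(G−2) factor is enough at the planned, near-equal cluster sizes; CR2 or Kauermann-Carroll is also acceptable. With very uneven recruitment the simple factor removes only part of the excess.
3. Cluster on the unit actually randomised, which is the practice where GPs share one, and count those units in the degrees of freedom.

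The cost is one sentence in the plan and about 2 to 3 points of power at 20 × 20 (81% to 82% falls to about 79%). The recruitment target of 46 GPs need not change.

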#### Handling of missing data and drop-outs

For the primary outcome, participants lost to follow-up will be considered as continuing smokers. We do not plan to replace drop-outs as the sample size calculation anticipates a 15% under-recruitment / dropout rate. Imputation will not be done for other variables of interest (weight, laboratory data). Participants lost to follow-up will be considered as continuing smokers without quit attempts/quit aids. For other secondary outcomes, data will be considered missing completely at random. The primary analysis will be an intention to treat analyses, with participants analysed according to their study arm, regardless of the completion rate. Participants lost to follow-up will be considered as continuing smokers.

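### Coding every patient lost to follow-up as having no quit attempt and no quit aid would, as written, overwrite events reported at an earlier contact

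*Protocol article*

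**What the plan says.** The rule is in the protocol article under *Handling of missing data and drop-outs*: "Participants lost to follow-up will be considered as continuing smokers without quit attempts/quit aids". For the remaining secondary outcomes the same section says: "For other secondary outcomes, data will be considered missing completely at random".

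The outcomes it governs are under *Secondary outcome measures*. One is the proportion of patients with one or more quit attempts in the six months after the baseline visit. The other is the "proportion of patients who use at least one quit aids (pharmacologic, electronic cigarette, or counselling sessions"). These correspond to secondary objectives 1 and 2.

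The contact schedule is in *Outcomes*, next to Fig. 3: "Follow-up questionnaires at 3 weeks, 3 months and 6 months will primarily be done by telephone". The content of each questionnaire is referred to Appendix Table 2, which is not part of the text at hand.

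*Withdrawal and discontinuation* adds: "Only baseline anonymised information will be retained for analysis once the patient/GP withdraws".

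**The concern.** An outcome of the at-least-one type is settled by a single positive report. A patient who reports a quit attempt at 3 weeks and cannot be reached afterwards has already met it, and nothing about that outcome is missing. The coding rule has no exception for this patient, so a programmer who follows it literally would score no. The withdrawal section leads to a similar place: interim reports already collected are dropped, and if withdrawals count as lost, the patient is again scored no.

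Coding missing as smoking has a rationale for abstinence, which is a status at 6 months that was not observed. The rationale does not carry over to an event that was observed before contact ended.

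At stake are the two outcomes that show whether the training changed what patients did on the way to quitting. Their proportions would be too low in both arms. If the arms lose different shares of patients, the comparison would also be biased, even with no true effect.

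**Working it through.** **Inputs from the protocol article** (*Sample size and power calculation*)
- Aid use, control: "10% get a specific pharmacologic aid or e-cigarette". Aid use, intervention: "20% will use a pharmacologic aid or e-cigarette".
- Loss: "Assuming 15% drop-out or under-recruitment by individual GPs".
- Primary outcome 4% vs 10.5%, two-sided 5% test, 80% power, intraclass correlation 0.03, 20 GPs per arm with 20 patients each.

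**Assumptions**
- The 15% is treated as patient loss, although the plan combines it with under-recruitment.
- The unequal splits (10%/20% and 20%/10%) are illustrations; the plan gives no loss by arm.
- Aid use among lost patients equals their arm's average.
- The planning rates for aid use omit counselling, which the outcome includes.
- No rate of quit attempts is given (the 20% and 40% in the plan are discussions of an attempt), so only aid use is worked through.

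**Step 1. The plan's own figure.** The pooled two-proportion formula for 4% vs 10.5% gives 249 per arm. The design effect is 1 + 19 × 0.03 = 1.57. Then 249 × 1.57 = 391 per arm, and 391 / 20 = 19.5 clusters, which rounds up to the stated 20. The sample size reproduces and is not in question here.

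**Step 2. Effect of the rule on aid use.** With true proportion p and loss d in an arm, coding all lost patients as non-users records p × (1 − d).

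| Loss control / intervention | Recorded control | Recorded intervention | Difference (points) | Risk ratio | Odds ratio |
|---|---|---|---|---|---|
| none | 10% | 20% | 10.0 | 2.00 | 2.25 |
| 15% / 15% | 0.10 × 0.85 = 8.5% | 0.20 × 0.85 = 17% | 8.5 | 2.00 | 2.20 |
| 10% / 20% | 0.10 × 0.90 = 9% | 0.20 × 0.80 = 16% | 7.0 | 1.78 | 1.93 |
| 20% / 10% | 0.10 × 0.80 = 8% | 0.20 × 0.90 = 18% | 10.0 | 2.25 | 2.52 |

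Odds ratio for the second row: (0.17/0.83) / (0.085/0.915) = 0.2048 / 0.0929 = 2.20.

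**Step 3. How much of this is overwriting.** The table charges the whole shortfall to overwriting. That holds only if all aid use by lost patients had been reported before loss. If half had been reported, counting those reports would record p × (1 − d/2):
- at 15%/15%, 9.25% vs 18.5%, a difference of 9.25 points;
- at 10%/20%, 9.5% vs 18%, a difference of 8.5 points.

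The rest of the gap to 10 points is then use that nobody reported, an ordinary missing-data problem.

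**Step 4. No true effect.** With the same p in both arms, the recorded difference is p × (control loss − intervention loss). A 10-point imbalance in loss creates a spurious difference of 0.10 × 0.10 = 1 point at a 10% rate and 0.20 × 0.10 = 2 points at a 20% rate.

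**Step 5. Power, for scale.** With 400 per arm and design effect 1.57 (effective 400 / 1.57 = 255), power for aid use is about 89% with nothing erased, 82% in the 15%/15% row and 67% in the 10%/20% row. The design effect is borrowed from the primary outcome, and the plan makes no power claim for aid use.

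**The case against.** The strongest reply is that nowhere does the protocol say that reported attempts or aids are overwritten. The rule sits in a section on missing data, and a yes recorded at 3 weeks is not missing. It may be meant only as a default for patients or time points without a report. Loss to follow-up is not defined, and its definition, with the derivation over three contacts, may be in a fuller document. Nor is it shown that attempts and aids are asked at every contact, since the questionnaire table is not at hand. All this stands: overwriting is what the wording produces if followed, not a stated intention. What does not fall away is that a rule without an exception has been fixed for outcomes that need one, and that the withdrawal section expressly keeps only baseline information.

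Four stronger readings are tempting and not supported:
- *The rule always shrinks the contrast.* It does not. With heavier loss in the control arm, the risk ratio rises to 2.25.
- *The between-arm effect is badly distorted whatever the loss.* Under equal loss the risk ratio does not move and the odds ratio, the scale of the planned logistic regression, moves only from 2.25 to 2.20. Material distortion needs unequal loss, which the protocol does not quantify. It cannot be excluded either: outcome assessors are not blinded, and patients are recruited after the GPs are randomised.
- *These are key secondary outcomes.* The protocol lists them without any such rank.
- *The missing-completely-at-random statement is a further error of consequence.* It is the strongest assumption available, but relabelling it would leave the planned mixed-model fits unchanged, so it is not pressed here.

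**Conclusion.** The point holds as a flaw in a stated coding rule. Read as written, it scores an observed attempt or aid as absent once the patient is lost, and the withdrawal wording drops interim reports in the same way.

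The certain consequence of following it is that proportions are understated in each arm: for aid use, by up to 1.5 points in control and 3 points in intervention at 15% loss. The difference falls from 10 to 8.5 points at most under that equal loss. The direction of bias under unequal loss depends on which arm loses more, with risk ratios of 1.78 and 2.25 in the two illustrations against a true 2.00.

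These sizes are worst cases under the assumptions listed with the calculation. The primary outcome, abstinence at 6 months, is untouched.

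**What to change.** 1. Define loss to follow-up, and score a quit attempt or quit aid as yes if it was reported at any completed contact before loss.
2. Limit the no default to patients with no positive report, and add a sensitivity analysis on the observed data under missing at random.
3. Reconcile the withdrawal section with this, so that follow-up data collected before withdrawal are kept where consent allows.

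Items 1 and 2 cost a few sentences and a change in derivation code, with no new data collection. If overwriting was never intended, one clarifying sentence settles the coding. Item 3 concerns participants' data rights and needs a short amendment; the protocol has already handled a change to withdrawal terms in that way.
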